#### 4.3.2 Histopathological CIN associated with HPV type

The section 4.4.2.1 of the RAP for the HPV-008 efficacy study (dated 8 August 2009) provides an overview of the histopathological endpoint determination process and the section 4.4.4.2 of the RAP details the case definition of histopathological endpoints.

A **histopathologically confirmed CIN** can be detected in the biopsy sample after colposcopy or in the excision specimen after treatment.

Histopathologically confirmed CIN include:

- **CIN1+:** Cervical intraepithelial neoplasia as CIN1, CIN2, CIN3, adenocarcinoma in-situ and invasive cervical cancer,
- **CIN2+:** Cervical intraepithelial neoplasia as CIN2, CIN3 adenocarcinoma in-situ and invasive cervical cancer.
- **CIN3+:** Cervical intraepithelial neoplasia as CIN3 adenocarcinoma in-situ and invasive cervical cancer.

The **histopathologically confirmed CIN associated with a given HPV type infection** will be defined at a subject level. A subject might have multiple lesions associated with different HPV types at the same time point or at different time points.

As for the HPV-008 efficacy study, the current study will include only histopathological endpoints which were confirmed by the study Endpoint Committee.

## 4.4 Determinant definitions

### 4.4.1 Reference cervical HPV infections used for definitions

The definitions of some determinants as well as their potential inclusion in the different statistical analyses will be based (when relevant) on the cervical HPV infections referenced in the analyzed endpoint:

- For a **histopathologically-confirmed CIN2+ (or CIN1+, or CIN3+) associated with the same HPV type as a previous confirmed 6-month persistent cervical HPV infection**, the reference cervical HPV infection will be the 6-month persistent infection,
- For a **histopathologically-confirmed CIN2+ (or CIN1+, or CIN3+) associated with the same HPV type as a previous cervical HPV infection (any cervical HPV infection)** the reference cervical HPV infection will be the cervical HPV infection,
- For the **clearance of a cervical HPV infection**, the reference cervical HPV infection will be the cervical HPV infection for which the clearance is observed,
- For a **first detected incident cervical HPV infection (or a first confirmed 6-month persistent cervical HPV infection)** following the start of sexual activity, the reference cervical HPV infection will be the first cervical HPV infection (or first confirmed 6-month persistent cervical HPV infection).

### 4.4.2 Clinical determinants

For each reference cervical HPV infection with a given HPV type over the 48-month follow-period, the following determinants will be defined:

- HPV type: 16; 18; 31; 33; 45; Other high risk HPV type; Other low risk HPV type.

The above categorization of HPV types will be used in the univariate and multivariable analyses. All HPV types will be considered individually in the tables presenting descriptive statistics by HPV type as well as high risk and low risk categories. The high risk (oncogenic) category is obtained by grouping together HPV types 16, 18, 31, 33, 35, 39, 45, 51, 52, 56, 58, 59, 66, and 68. The low risk (non-oncogenic) category is obtained by grouping together HPV types 6, 11, 34, 40, 42, 43, 44, 53, 54, 70 and 74. In some cases, the category “No cervical HPV infection” will be added in the categorization for univariate and multivariable analyses.

- HPV infection category: 6-month persistent, less than 6-month persistent, transient, last visit detected.
- Previous cervical HPV infection: No; Yes, with at least one high risk HPV type; Yes, with only low risk HPV type.
- Histopathologically-confirmed CIN2+ (or CIN1+, or CIN3+) following the reference cervical HPV infection, associated with a different HPV type, and preceding the CIN2+ (or CIN1+, or CIN3+) associated with the same HPV type as the reference infection (i.e. date of CIN2+ (or CIN1+, or CIN3+) following the reference infection strictly inferior to date of CIN2+ (or CIN1+, or CIN3+) associated with the same HPV type as the reference infection): No; Yes, with at least one high risk HPV type; Yes, with only low risk HPV type.

- Histopathologically-confirmed CIN2+ (or CIN1+, or CIN3+) preceding the reference cervical HPV infection, associated with a different HPV type : No; Yes, with at least one high risk HPV type; Yes, with only low risk HPV type.
- Co-infection with other HPV types (concomitant cervical HPV infections): No; Yes, with at least one high risk HPV type; Yes, with only low risk HPV type.

Co-infection with other HPV types is defined as the detection of these HPV types at time of the onset of the reference cervical HPV infection or, if this infection is persistent, during the duration of the reference cervical HPV infection until its end or until the occurrence of the event, whichever comes first.

Consequently any cervical HPV infection which onset is prior to the onset of the reference cervical HPV infection will be considered as a previous cervical HPV infection and any cervical infection which onset if after the end of the reference cervical HPV infection and before the occurrence of the event will not be considered as a co-infection.

However, when analyzed as time-varying covariables, co-infections will be considered until the occurrence of the event (e.g., lesion).

The following determinants will be defined for the purpose of analyzing immunosubset but they won't be included as covariates in the multivariable models:

- Serology status (based on ELISA) at study entry (Month 0) for HPV-16: Negative; Positive.
- Serology status (based on ELISA) at study entry (Month 0) for HPV-18: Negative; Positive.

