### **6.2.4.2 Analysis unit**

The statistical unit for this analysis will be the 6-month persistent cervical HPV infection for which it is assessed that a following histopathologically-confirmed CIN2+ (or CIN1+, or CIN3+) associated with the same HPV type is detected.

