### 6.2.5.2 Analysis unit

The statistical unit for this analysis will be the cervical HPV infection for which it is assessed that a following histopathologically-confirmed CIN2+ (or CIN1+, or CIN3+) associated with the same HPV type is detected.

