### 6.2.6.2 Analysis unit

The statistical unit for this analysis will be the cervical HPV infection for which the clearance is assessed.

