#### **6.2.7.2 Analysis unit**

The statistical unit for this analysis will be the subject.

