### 6.2.7.3 Event variable

The analyzed event - first incident cervical HPV infection (or a first confirmed 6-month cervical HPV infection) - will be analyzed by means of a binary variable with the following categories:

- 1 = First detected cervical infection following the start of sexual activity
- 0 = No detection of cervical HPV infection following the start of sexual activity

The event will be determined as showed with the following examples (See section 8.4.3 for more details):

| Sub-
ject* | Detected cervical HPV infections**
over the follow-up period
(in chronological order)                                                                                                                   | Subject
included
in analysis
population | Event
(first
infection)
(0 = No /
1 = Yes) | Event
(first
persistent)
(0 = No /
1 = Yes) |
|---------------|---------------------------------------------------------------------------------------------------------------------------------------------------------------------------------------------------------------|--------------------------------------------------|--------------------------------------------------------|---------------------------------------------------------|
| A             | -                                                                                                                                                                                                             | Yes                                              | 0                                                      | 0                                                       |
| B             | Transient infection associated with HPV type X
Transient infection associated with HPV type Y                                                                                                              | Yes                                              | 1                                                      | 0                                                       |
| C             | Transient infection associated with HPV type X
Transient infection associated with HPV type Y
12-month persistent infection associated with HPV type Y                                                  | Yes                                              | 1                                                      | 1                                                       |

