| #1 | ◇ (12 months prior month 0) | HPV 16  | HPV 16   |          |          |          |          |          | n        | NA    |               | 
 
Subject #1 reported beginning of sexual activity one year before month 0. She had a first 6-month persistent HV16 cervical infection detected at month 6.
 
She is not included in the analysis.
 
                                                                                                                                                                                                                                                                               |
| #2 | ◇ (6 months prior month 0)  |         |          |          |          |          |          |          | y        | n     | 54 (censored) | 
 
Subject #2 reported beginning of sexual activity 6 months before month 0. She did not have any cervical HPV infection throughout the 48-month follow-up period.
 
She is included in the analysis with a censored time-to-event value of 54 months and HPV type = "No cervical HPV infection".
 
                                                                                                                                                                                 |
| #3 |                             | ◇       |          | HVP16    |          |          |          |          | y        | n     | 18            | 
 
Subject #3 reported beginning of sexual activity at month 6. She had a first transient HV16 cervical infection detected at month 24.
 
She is included in the analysis of time to first incident cervical HPV infection (but not in the analysis of time to first 6-month persistent cervical HPV infection) with a time to event value of 18 months and HPV type = 16.
 
                                                                                                        |

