### 9.5.3 Analysis of time to first detected incident cervical HPV infections

|                                                           | Covariates                                       | Type    | Categories                                               | Time-dependent | Comment                      |
|-----------------------------------------------------------|--------------------------------------------------|---------|----------------------------------------------------------|----------------|------------------------------|
| Demographic characteristics
(defined at subject level) | Region                                           | Class   | Europe
Asia Pacific
Latin America
North America | No             |                              |
| Behavioral Covariates
(defined at subject level)       | Smoking                                          | Ordinal | [0-0.5[ pack/year
≥0.5 pack/year                      | No             |                              |
|                                                           | Age at beginning of sexual activity (years)      | Ordinal | Never had sexual intercourse
<15
15-17
18-25    | No             |                              |
|                                                           | Number sexual partner during the previous year   | Ordinal | 0
1
2-3
≥4                                      | No             |                              |
|                                                           | Marital status                                   | Binary  | Living or lived with a partner
Single                 | No             | Re-assessed at yearly visits |
|                                                           | At least one previous pregnancy                  | Binary  | No
Yes                                                | No             | Re-assessed at each visit    |
|                                                           | Hormones for contraception or another indication | Binary  | No
Yes                                                | No             | Re-assessed at each visit    |
|                                                           | Intra-uterine device                             | Binary  | No
Yes                                                | No             | Re-assessed at each visit    |

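### SAP 4.4.2 adds a no-infection level to HPV type for modelling; it can arise only in the time-to-first-infection analysis, where it restates the outcome and contradicts 6.2.7.5, 9.5.3 and 9.5.4

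*SAP*

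**What the plan says.** **The level.** SAP 4.4.2 defines HPV type with seven levels (16, 18, 31, 33, 45, other high risk, other low risk). It then says that in some cases a further level, *No cervical HPV infection*, "will be added in the categorization for univariate and multivariable analyses". The cases are not named. Descriptive tables are covered by a separate sentence in the same paragraph.

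**The analysis units.**
- Persistent infection to lesion (6.2.4.2): "The statistical unit for this analysis will be the 6-month persistent cervical HPV infection".
- Any infection to lesion (6.2.5.2): "The statistical unit for this analysis will be the cervical HPV infection for which it is assessed".
- Clearance (6.2.6.2): "The statistical unit for this analysis will be the cervical HPV infection for which the clearance is assessed".
- Time to first infection (6.2.7.2): "The statistical unit for this analysis will be the subject".

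**The first-infection outcome.** Section 6.2.7.3 codes a woman without the event as "0 = No detection of cervical HPV infection following the start of sexual activity".

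**The worked examples (9.4.3).** Of subject #2, who has no infection, the annex says "She is included in the analysis with a censored time-to-event value of 54 months and HPV type" equal to the no-infection level. Subjects #3 and #5 get HPV type 16, the type of their first infection.

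**The determinants for this analysis.** Section 6.2.7.5 admits only determinants that start before the first detected infection. The list headed "Analysis of time to first detected incident cervical HPV infections" (9.5.3) contains region and behavioral covariates. The list in 9.5.4, for first persistent infection, adds previous infection. Neither list contains HPV type. (6.2.7.5 calls them 8.5.3 and 8.5.4; the annex numbers are 9.5.3 and 9.5.4.)

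**The concern.** A determinant must be capable of being known before the outcome, or at least of being something other than the outcome. If the no-infection level is used where 9.4.3 places it, one level contains only women without the event and every other level is defined by the infection that is the event. A comparison across such levels carries no information about what predisposes women to infection.

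The result could still look like a finding. A very large separation of Kaplan-Meier curves by HPV type would come from the coding alone. In a multivariable model, the same variable would account for which women have events before any real determinant is considered. The SAP gives two sets of instructions, and an analyst who follows the first gets an invalid result.

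**Working it through.** **Step 1: where can the level occur?**

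| Analysis | Unit | Population requires an infection? | No-infection level in the covariate list? |
|---|---|---|---|
| 6.2.4 persistent infection to lesion | infection | yes (6.2.4.1) | no (9.5.1, seven levels) |
| 6.2.5 any infection to lesion | infection | yes (6.2.5.1) | no (9.5.1, seven levels) |
| 6.2.6 clearance | infection | yes (6.2.6.1) | no (9.5.2, seven levels) |
| 6.2.7 time to first infection | woman | no | HPV type not listed (9.5.3, 9.5.4) |

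Only 6.2.7 can produce a record without an infection. The sentence in 4.4.2 has no other analysis to apply to.

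**Step 2: what does the level mean there?** Section 4.4.1 makes the first infection itself the reference infection, so HPV type is the type of the event. Section 6.2.7.1 removes women whose infection precedes the start of sexual activity. For first incident infection this leaves: level = no infection if and only if event = 0, and any type if and only if event = 1.

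The examples follow this. Subject #2 is censored at 48 + 6 = 54 months, which reproduces the stated figure, and carries the no-infection level. Subject #5 has the event at 24 − 6 = 18 months and carries type 16. Subject #3 has the same pattern as #5 and an uncensored 18 months, but its event column says no; that looks like a slip.

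For first persistent infection the identity is not literal. In 6.2.7.3, subject B has only transient infections and is event-free for that endpoint, so not every event-free woman is infection-free. (9.4.3 instead leaves women like #3 and #5 out of that analysis, a separate inconsistency.) The type of the event infection is outcome-defined for this endpoint too.

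**Step 3: what would the planned methods return?** Section 6.2.7.5 takes over the log-rank test and Cox models of 6.2.4.5. At event time j, let n1j be the women at risk who will become infected, n0j those who will be censored uninfected, and nj = n1j + n0j.

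- *Log-rank.* Every event falls in the infected level, so observed minus expected is 1 − n1j/nj = n0j/nj, never negative. Then z = Σ(n0j/nj) / √Σ(n0j·n1j/nj²). All terms add in one direction, whatever the data. With a handful of events z could still miss the cut-off.
- *Cox.* Each event contributes exp(β)/(n1j·exp(β) + n0j). This rises with β whenever n0j > 0, so the partial likelihood has no finite maximum and the hazard ratio is not estimable.

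**Step 4: simulation.** Assumptions, not taken from the SAP: 20, 50, 100 or 300 women; infection hazard 0.005 or 0.02 per month; censoring uniform on 6 to 54 months; all types merged into one infected level; up to 200 data sets in each of 8 settings.

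| Quantity | Result over the 8 settings |
|---|---|
| Log-rank rejection, outcome-defined level | 100% of usable runs in every setting |
| Log-rank rejection, unrelated baseline covariate | 3.3% to 5.0% |
| Median fitted hazard ratio | about 1e12 to 2.6e13, many fits not converging |
| Median likelihood-ratio statistic, 1 df | 12.9 to 315.0 |
| Median model-based Wald p | about 1.0 |

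Section 6.2.4.5 names robust sandwich variance. A second simulation (50 to 1,000 women, same hazards and censoring, about 300 runs per setting) gave a bounded robust standard error of about 0.08 to 0.32 while the coefficient kept growing. At hazard 0.02 the log hazard ratio was about 10 after 8 Newton steps and about 14 after 12. The robust Wald test rejected in 100% of runs, against 4.6% for an unrelated covariate. The robust output would thus look decisive around a hazard ratio set by where the iteration stopped.

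**The case against.** The strongest objection is that the sections governing this analysis already exclude the comparison. Section 6.2.7.5 is the methods text for first infection, and the type of the event infection cannot start before the first infection. Section 6.1.2 makes inclusion depend on what a determinant means for the endpoint, uses time to first infection as its example, and defers to the lists. Those lists omit HPV type. Section 4.4.2 is a general definitions section that names no analysis. Annex 9.4 is about determining events and times, so its HPV-type label may be no more than a record label, and 6.2.3.1 does provide for describing endpoints by HPV type.

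Most of this stands. A reader might infer that the SAP plans a test that is bound to be significant. The document does not support that: it contradicts itself, and on the more specific text the test is not run. The simulation shows what the coding would do, not that it will be used. A reader might also infer that every Cox test would reject. That is too strong: the failure is a non-estimable hazard ratio, and the model-based Wald test is uninformative. The effect on the other determinants' hazard ratios was not computed.

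The objection does not remove the conflict. The sentence in 4.4.2 refers expressly to univariate and multivariable analyses. The example in 6.1.2 excludes determinants linked to infections after the first, which does not clearly cover the first infection's own type. No analysis remains in which the sentence could validly apply.

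**Conclusion.** The point holds as a contradiction to be resolved. Section 4.4.2 prescribes a modelling level that, by unit and population, can occur only in 6.2.7, and 9.4.3 shows it assigned there. Sections 6.2.7.5, 9.5.3 and 9.5.4 exclude HPV type from those models.

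The size depends on which text is followed. Under 4.4.2, for first incident infection, the log-rank test is significant by construction and the Cox hazard ratio cannot be estimated. Under the other sections there is no effect, because the comparison is not made. The structural argument rests on the SAP's own coding; only the simulated rates depend on assumed sample sizes, hazards and censoring. For first persistent infection the no-infection level is not identical to being event-free under 6.2.7.3, but the type of the event infection is still not a valid covariate.

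The reach is limited to the secondary first-infection analyses, which section 1 assigns to a stand-alone report. The primary analysis, the other lesion analyses and the clearance analysis are untouched.

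**What to change.** 1. In 4.4.2, delete the sentence on the no-infection level, or limit it to descriptive tables.
2. In 6.2.7.5, state that the HPV type of the event infection is not a covariate in either first-infection analysis, in line with 9.5.3 and 9.5.4.
3. In 9.4.3, mark the HPV-type label as descriptive only, and check the event entry for subject #3 at the same time.

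If type-specific results are wanted, a separate time-to-first-infection analysis per HPV type, with all eligible women at risk, would be valid; this is optional.

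The cost is SAP wording. No new data are needed, and section 7 schedules the first-infection analysis after the other planned endpoints.

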#### **4.4.3 Behavioral determinants**

The following behavioral determinants will be defined at subject level using data from the last yearly questionnaire preceding the date of the detection of the reference cervical HPV infection:

- Cigarette Smoking: number of packs per year (one pack will be considered as equivalent to 20 cigarettes):
  - [0;0.5[ pack year (women who never smoked i.e. never tried a cigarette or smoked <1 pack per day for less than 6 months) ;
  - $\geq 0.5$  pack year (women who smoked  $\geq 1$  pack per day for less than 6 months or smoked <1 pack per day for 6 months or more or smoked  $\geq 1$  pack per day for 6 months or more)
- Age at first intercourse (years): Never had sexual intercourse; <15; 15-17; 18-25.
- Number of sexual partners: 0; 1; 2-3;  $\geq 4$ .
- Marital status: Living or lived with a partner; Single.
- At least one previous pregnancy: No; Yes. Parity will also be explored.

The following determinants will be assessed at subject level using data from the CRF of the most recent visit preceding the reference cervical HPV infection:

- Hormones for contraception or another indication: No; Yes.

- Intra-uterine device: No; Yes.
- Sterilized: No; Yes.
- *Chlamydia trachomatis*: No; Yes.

The presence of *Chlamydia trachomatis* at visits following baseline will be derived from the AEs collected in HPV-008 study using the following MedDRA codes for *Chlamydia*: '10008538', '10018185', '10053028', '10061041', '10062780', '10062784', '10064525', '10067186', '10067198'.

In addition, results from *Chlamydia trachomatis* DNA yearly screening will also be used.

